## Abstract

**Background:**

A high number of individuals report suffering from physical and psychological sequelae symptoms after COVID-19—the so-called post COVID-19 condition. Commonly reported complaints include physical symptoms such as fatigue, headache, attention and concentration deficits or dyspnea and anxiety, symptoms of post-traumatic stress, or depression. Evidence-based treatment recommendations are still lacking up to this point. Associations between physical and psychological symptoms in chronic diseases are known for a long time. Support in coping with the disease and improvement of self-efficacy can have a positive effect on the course of diseases. For this reason, we designed a randomized, controlled explorative intervention trial as a treatment of bodily distress disorder in COVID-19 recovered persons.

**Methods:**

Patients with a post COVID-19 condition meeting to the criteria of the WHO, along with a bodily distress disorder, are randomized in an intervention and control arm (TAU). Randomization takes place after a diagnostic interview, screening, and informed consent. In total, 60 patients will be included in the trial (30 per group). The intervention group receives a cognitive behavioral therapy as a video-conference-based group therapy (6 weeks) and mobile, respiratory biofeedback treatment (for 4 weeks). At several time points, both groups are assessed in terms of psychological and physical health status, treatment expectation, and satisfaction with the intervention. Furthermore, they will get biofeedback examination appointments. The primary outcome is the change in self-efficacy; secondary outcomes include assessed parameters of mental health, somatic symptoms, and satisfaction with the intervention. Data will be analyzed primarily using R and SPSS.

**Discussion:**

The randomized, controlled, explorative intervention trial POSITIV is one of the very first interventions for patients with post COVID-19 condition and psychological burden due to their different symptoms. The aim of the study is to generate new evidence and help patients to cope with the disease and thus, increase their quality of life and reduce symptomatology. We expect with a high probability that the patients’ self-efficacy and health status will improve as a result of the intervention.

**Trial registration:**

German Clinical Trial Register (DRKS); DRKS-ID: DRKS00030565. Registered on December 22, 2022.

**Supplementary Information:**

The online version contains supplementary material available at 10.1186/s13063-025-08842-6.

## Background

Many people who recovered from COVID- 19 described somatic and psychological sequelae symptoms weeks and months after an acute COVID- 19 infection [1]. Current data estimate that 10% of all who were infected suffer from such sequelae symptoms [2]. Due to the heterogeneity and novelty of the disease, there was no clear medical definition for prolonged COVID- 19 symptoms for a long time [3]. In late 2021, the World Health Organization (WHO 2022) coined the term “post COVID- 19 condition” [4]. It is defined as a disease or impairment that occurs in persons who have experienced a SARS-CoV- 2 infection, and which results in symptoms usually occurring within 3 months after COVID- 19. Such symptoms are expected to persist for at least 2 months and must not be explainable by any other diagnosis [4].

In clinical practice, the post COVID- 19 condition presents as a heterogeneous syndrome. According to systematic reviews, the five most common symptoms are fatigue (58%), headache (44%), attention deficit symptoms (27%), hair loss (25%), and dyspnea (24%) [5, 6]. Insomnia, anxiety, symptoms of post-traumatic stress disorder, depression, and somatization have been reported as the most common psychological symptoms.

Already at early stages of the pandemic, it became apparent that COVID- 19 patients experience psychological distress both during and after the acute phase of illness [6–11]. Multiple factors were discussed to be relevant. Among others, authors have mentioned insecurities, fears about the consequences of the infection, stigmatization, concern about having infected another person, social isolation, and/or the stressful and unfamiliar experience or situation during inpatient (intensive care) hospitalization [12–14]. Patients often report psychological burden due to the prominent somatic symptoms, which are, in turn, accompanied by concerns about the disease progress and its impact on their daily life.

In fact, chronic somatic diseases often cause psychological distress. Typical diseases that potentially cause massive psychological distress include oncological, but also neurological and cardiological illnesses.

The treatment and diagnostic guidelines for such oftentimes chronic diseases already suggest psychological treatment or care for patients who wish to receive support [15, 16]. Moreover, the German guideline for post COVID- 19 treatment explicitly mentions psychosomatic treatment options [17].

Psychological burden due to an underlying somatic disease may lead to a bodily distress disorder also called somatic symptom disorder, as defined in the DSM- 5 as well as ICD- 11 [18–20]. Due to the versatility of symptoms on both, the physiological and psychological level, an interdisciplinary treatment concept is necessary. Treatment should be symptom- and patient-oriented. A staged concept depending on the severity and complexity of the course is preferable.

At the moment, there is no science-based knowledge on psychological treatment of the patients with a post COVID- 19 condition with psychological burden. However, intervention studies for bodily distress disorders—mostly in combination with somatic diseases—show the most promising results up to this point when including cognitive behavioral therapy (CBT)-based methods, as well as therapies that include the direct regulation of the stress, arousal, and bodily sensations [21, 22].

With this knowledge, we have designed our randomized controlled study, which focuses on videoconference-based CBT-based group intervention and a mobile respiratory biofeedback treatment. This integrative intervention will focus on strengthening patient’s self-efficacy. The aim of this RCT study is to generate new evidence in the treatment of patients with post COVID- 19 specifically targeting the psychological burden that goes along with it. We intend to help patients to cope with the disease and the accompanying repercussions via CBT-based and biofeedback-based interventions. Here, we use self-efficacy experience as a primary outcome measure. In the second place, we will assess the patient’s mental health and somatic symptoms as well as intervention’s acceptability by measuring treatment satisfaction, expectation, feasibility, and acceptance directly.

## Methods/design

### Study design

The study is an exploratory randomized controlled trial with two parallel study arms. After screening and recruitment, participants will be randomized into the two study groups. Participation is voluntary. The recruitment itself started in October 2022.

The study protocol is based on the SPIRIT guidelines [23]. The checklist can be found in the appendix.

Participants receive pre-treatment assessments at baseline (T0) and post-treatment (T1), as well as at three follow-up assessments (3, 6, 12 months after the intervention; T2–T4). Patient data is collected and stored in strictly pseudonymous form. Participants can decide to refrain from participation at any time. In this case, participants will be asked to complete an assessment regarding reasons, expectations, and changes (see Fig. 1).

**Fig. 1 Fig1:**
[figure not shown]
Flow chart of the POSITIV trial

### Participant recruitment

Recruitment takes place via outpatient clinics (usually general physicians and post COVID- 19 specialists), newspaper articles, social media, self-help groups, by telephone or e-mail, as well as by mail. The Clinic for Psychosomatic Medicine and Psychotherapy (LVR-University Hospital) with support of the Department of Infectious Diseases (University Hospital Essen) was responsible for recruitment. The recruitment started in October 2022 and is scheduled to be completed in September 2023.

### Inclusion criteria

We include adult participants (18 years or older) with sufficient knowledge of German language to allow active participation in psychological interventions. Interested participants must meet the diagnostic criteria for bodily distress disorder (see ICD- 11 or DSM- 5 criteria) [19, 20] and the criteria for a post COVID- 19 condition (WHO Delphi Consensus diagnostic criteria) [4]. Bodily distress disorder (ICD- 11) involves excessive focus on distressing physical symptoms, accompanied by disproportionate worry or health-related behaviors. Symptoms persist for several months, significantly impairing daily functioning [24]. Furthermore, symptom severity does not exceed a critical level so that an inpatient treatment is necessary. Participants must give written informed consent.

Inclusion interviews are always conducted in the outpatient clinic for Psychosomatic Medicine and Psychotherapy (LVR-University Hospital Essen) by the same female physician who also conducts the experimental interventions (videoconference-based cognitive behavioral group intervention). Patients should not participate another bio- or neurofeedback intervention during the study.

### Intervention: mobile biofeedback treatment and videoconference-based cognitive behavioral group intervention

The first part of the intervention includes element of cognitive behavioral therapy. The therapy is conducted online as a group therapy with about four up to seven participants. It takes place weekly for 6 weeks. One therapy session lasts 60 min. In the six modules, the participants focus on the following topics: stress/distress, resources, emotions, behavior, thoughts and recognizing own needs and limits, future perspectives and goals. The videoconference systems (*samedi GmbH*; Berlin, Germany or *RED Medical* Systems GmbH; Muenchen, Germany) allow patients to participate in therapy from home. Both digital providers are approved by health insurances for online psychotherapy.

The second part of the intervention is a mobile respiratory biofeedback treatment. The focus on respiration was chosen because of the frequently named symptom of dyspnea in post COVID- 19 patients. The respiratory biofeedback treatment is performed in the patients’ home environment (4 weeks), and the behavioral cognitive therapy takes place as a videoconference-based group intervention (6 weeks). The mobile biofeedback devices (*eSense Respiration*) are a *Mindfield® Biosystems Ltd.* ([name]; Gronau, Germany) product. The product includes a breathing sensor—which monitors breathing frequency, amplitude, and its pattern in connection with *eSense skin response*. A mobile application makes it possible to perform the biofeedback training at home, although support by the provider will be offered. Before starting the respiratory biofeedback treatment, patients receive a detailed technical education with an additional written instruction.

The feedback itself might be visualized in different tasks, such as bar feedback, curve feedback, video feedback, music feedback, tone feedback, tactile feedback through vibration, or free training. Patients are recommended to exercise at least twice a week for 15 min each time. Changes and successes are recorded by the app and can be evaluated later.

### Control intervention: TAU

A TAU-based control group was selected as control group. Patients will have access to standard healthcare during the trial. The treatment as usual (TAU) includes all currently existing measures of support and treatment available to patients in somatic and psychosomatic care (e.g., outpatient individual or group psychotherapy, (partial) inpatient psychosomatic treatment, nutritional counseling, social work, physical therapy. self-help group, online interventions).

### Outcomes

The primary aim is to evaluate an intervention for the treatment of bodily distress disorder in COVID- 19 recovered persons. This will address an existing gap in the medical care system in Germany and provide new evidence in the treatment of a bodily distress disorder going along with a post COVID- 19 condition.

#### Primary outcome measure

The primary outcome is the change of self-efficacy at the end of the treatment (T1). To assess the self-efficacy of the participants, the 10-item *General Self-Efficacy Scale* [GSES] is used [25]. The scale was created to capture of perceived self-efficacy which reflects an optimistic self-belief. This can be a positive resource factor for resistance in accomplish new or difficult tasks or cope with new burden. We used the German version of the assessment [25].

#### Secondary outcomes measure

The secondary outcomes are used to monitor of assessed parameters on mental health, somatic symptoms, and quality control of the intervention. This includes (1) distress, (2) depression, (3) anxiety, (4) quality of life, (5) symptoms of a post-traumatic stress disorder, (6) sense of coherence, (7) somatic symptom burden, (8) symptoms of somatic symptom disorder, (9) symptoms of post COVID- 19, (10) patient satisfaction, (11) patient motivation, and (12) patient expectation (Table 1).

**Table 1 Tab1:** Overview of contents of the assessment at different points in time

Measures	Baseline T0	End of treatment T1	Follow-up assessments T2–T4	Dropout assessment
**Primary outcome measure**				
General Self-Efficacy Expectancy Scale [GSES]	x	x	x	
**Secondary outcomes measure**				
Distress Thermometer	x	x	x	x
The Patient Health Questionnaire Depression Scale [PHQ- 8]	x	x	x	x
Generalized Anxiety Disorder Scale- 7 [GAD- 7]	x	x	x	x
The World Health Organization Quality Of Life Questionnaire [WHOQOL-BREF]	x	x	x	x
The Revised Impact of Event Scale [IES-R]	x	x	x	
Sense of Coherence Scale—Leipzig Short Form [SOC-L9]	x			
Somatic Symptom Scale- 8 [SSS- 8]	x	x	x	x
The Somatic Symptom Disorder—B Criteria Scale [SSD- 12]	x	x	x	x
The course and symptoms of the COVID- 19 infection	x			
Post COVID Syndrome [PCS] Score	x	x	x	x
**Measures exclusively for intervention group**				
Client Satisfaction Questionnaire [CSQ]		x		x
Motivation regarding the intervention	x	x	x	
Expectations regarding the intervention	x	x	x	
Engagement with the exercises		x	x	x
Reasons for dropout				x

The variables are as followed:Distress: The *Distress Thermometer* is an 11-point visual analog scale which inquires the patients to indicate their distress over the past week (including today). The scale ranges from 0 (no distress) to 10 (worst-possible distress) [26].Depression: The *Patient Health Questionnaire Depression Scale* [PHQ- 8] has eight items and is designed to diagnose and determine the severity of depression [27].Anxiety: This is measured with the *Generalized Anxiety Disorder Scale- 7* [GAD- 7]. The GAD- 7 is a seven-item assessment used to evaluate generalized anxiety disorder [28].Quality of life: The *World Health Organization Quality Of Life Questionnaire* [WHOQOL-BREF] assesses quality of life [29]. It was developed in 1998 as a shortened version of the WHO-QOL- 100 and includes four domains related to quality of life: physical health, mental health, social relationships, and environment.Symptoms of a post-traumatic stress disorder: The *Revised Impact of Event Scale* [IES-R] captures symptoms and typical reactions to stressful events such as natural disasters or serious accidents on three subscales: intrusions, avoidance, and overexcitement [30]. The IES-R is well suited for measuring symptom severity and has satisfactory psychometric characteristics. In our study, the questions in the IES-R regarded the COVID- 19 infection.Sense of coherence: This is considered a dispositional coping resource that makes people more resilient to stressors. The *Sense of Coherence Scale—Leipzig Short Form* [SOC-L9] is used to measure the sense of coherence of patients and subjects in the sense of Antonovsky [31]. It is a one-dimensional scale consisting of 9 items.Somatic symptom burden: The burden due to somatic symptoms is measured by the *Somatic Symptom Scale- 8* [SSS- 8] [32]. It is a validated patient-reported outcome assessment.Symptoms of somatic symptom disorder: The *Somatic Symptom Disorder—B Criteria Scale* [SSD- 12] is an instrument that operationalizes the psychological characteristics of a Diagnostic and Statistical Manual of Mental Disorders, Fifth Edition somatic symptom disorder [33]. It consists of 12 items.Symptoms of post COVID- 19: To assess the post COVID- 19 symptoms of the participants, we used the *Post COVID Syndrome (PCS) Score* [34].Patient satisfaction: The *Client Satisfaction Questionnaire* [CSQ] is a screening assessment consisting of 8 items that measures patient satisfaction [35].Patient motivation: We asked patients to estimate their motivation regarding the biofeedback treatment and group intervention on a scale from 0 to 100 (none, very high). Moreover, participants were asked to indicate, how often they performed the exercises presented the group intervention or biofeedback treatment (0 = almost never; 5 = almost daily).Patient expectation: Furthermore, the patients were asked about their treatment-related expectations. These questions were scaled from 0 to 100 (none, very high). In an open question, respondents were asked about content in group therapy that they particularly liked or disliked.

### Biofeedback examination

Biofeedback assessment will take place at measurement before the group intervention, between the group intervention and the biofeedback training, and after the biofeedback training (week 0, 6, and 10). Different physiological measures will be assessed using the Nexus- 10 device (MindMedia, Herten, Germany): respiratory rate, blood volume pulse, shoulder–neck electromyography, and electroencephalography. The diagnostic assessment follows a 14-min protocol. Participants will undergo a 2-min baseline measurement, 2-min stress induction by using the Stroop test [36, 37], 2-min relaxation (beach images and calm music), 2-min stress induction by mental arithmetic (based on Kirschbaum et al.) [37], 2-min relaxation (beach images and calm music), 2-min stress induction by reporting a recent stressful event, and 2-min relaxation (beach images and calm music [36, 37]).

### Sample size calculation

The power analysis was performed for a 2 (between-subjects, treatment vs. control) × 5 (within-subject, measurements T0–T4) design where the primary focus was the interaction effect between the treatment and the time variable. We used G*Power [38]. In order to be able to find an effect of *η*
_*p*_
^2^ = 0.03 with a test power of 1 − *β* = 0.80, which falls between what is considered a small and medium effect size [39], a total sample of 44 participants is needed.

Based on Cooper and Conklin, we assume a non-negligible dropout rate [40]. Therefore, we planned to assign 30 participants to both the treatment and control conditions, summing to a total sample of *n* = 60.

### Data management, data storage, and dissemination

The data are collected in a pseudonymous fashion and will be stored for 10 years (in conformance with the Good Clinical Practice guidelines [25]). The study will be subject to European Data Protection Regulation (EU-DSGVO). In detail, patient records will be kept in accordance with hospital policy, and access to stored data will be restricted to authorized personnel. We will publish key study results in an open-access, peer-reviewed journal and make publicly available via the Clinical Trials Registry. In addition, we will present the results at conferences and communicate the scientific results in plain language through press releases, social media, or patient forums.

The Project Management Group will meet weekly to review the trial conduct.

After the findings of the study are published, we want to make the collected data available in anonymized form upon reasonable request. We will retain the statistical analysis plan and relevant documents and make them available upon request. Overall, the patient consent forms include a section addressing the above aspects of data storage and sharing.

### Randomization and blinding

For randomization, a standard computer algorithm is used with the function of a 1:1 randomization. Randomization is carried out by the person conducting the inclusion interview. Due to the study design, a complete blinding for patients will be impossible.

However, the final analysis is performed by a blind analyst to ensure objective evaluation.

### Statistical methods

The aim of the study is to analyze the efficacy of the intervention in terms of improvement of self-efficacy as well as mental and physical health. This will take place in comparison between the intervention and control group. In the evaluation, we will perform an analysis of covariance (ANCOVA) with the outcome measured at T1 and the baseline scores of T0.

First of all, the analyses will be performed according to the intention-to-treat principle. Missing data will be imputed. Therefore, SPSS multiple imputation, module employing “monotone missing pattern” and incorporating complete data for sex, age, and baseline measurements of primary and secondary outcomes are used. We do not plan interim analyses.

Secondly, to evaluate the sustainability of the effects in comparison of both groups (between-subject factor) and of the different measurement points (T0–T4; with-subject factor) mixed ANOVAs will be conducted. In case of massive violations of normality, we will resort to robust methods such as generalized estimating equations. In case of violation of assumption of sphericity, we will use Huynh–Feldt or Greenhouse–Geisser corrections. Further descriptive analyses will assess treatment motivation, expectations, satisfaction, clinical data, and sociodemographic data. To illustrate potential group differences, *t*-tests and χ^2^ tests will be used. In case of non-normality or small cell sizes, the Mann–Whitney *U* tests or Fisher’s exact tests will be used. Further potential exploratory analyses might include subgroup comparisons, such as sex differences, dropouts, or participants who have the most benefit. Third, we would like to explore possible correlations and association patterns using regression analysis or network analysis. The documentation of adverse events and serious adverse events is conducted in separate tables and line listings for comprehensive analysis to ensure the highest level of safety, although we do not anticipate any serious or adverse events. However, should any unexpected serious adverse events occur (such as suicidal risks or severe depressive symptoms), participants will have access to expert consultation from the study team to ensure they receive the necessary support.

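### The printed imputation model omits treatment arm, so imputed T1 scores carry no group difference and the primary effect is biased toward zero

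*Protocol article*

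**What the plan says.** Four statements, all in Statistical methods of the protocol article, bear on this point.

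- Primary analysis: "we will perform an analysis of covariance (ANCOVA) with the outcome measured at T1 and the baseline scores of T0". The preceding sentence makes this a comparison of the intervention and control groups. Under Primary outcome measure, the outcome is GSES at the end of treatment.
- Analysis set: "the analyses will be performed according to the intention-to-treat principle", with missing data imputed.
- Imputation: the SPSS multiple imputation module with the "monotone missing pattern" option, "incorporating complete data for sex, age, and baseline measurements of primary and secondary outcomes are used".
- Later visits: for T0–T4, "mixed ANOVAs will be conducted".

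Randomization and blinding adds that a blinded analyst does the final analysis. Sample size calculation expects appreciable dropout but gives no rate. No section says how many patients are expected to lack a T1 score.

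**The concern.** An imputation model should contain every variable that the analysis model tests. Here the ANCOVA tests arm, and the printed imputation model does not contain it. A missing T1 score in the intervention arm is then predicted from the same regression as one in the control arm. On average, imputed patients contribute no difference between arms beyond what their baseline scores explain, so they dilute the difference seen among observed patients.

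The primary intention-to-treat estimate is at stake. In a trial of 60, a real benefit could be reported as smaller than it is, or as no effect. Blinding makes the gap easier to overlook, because a blinded analyst who follows the printed list has no prompt to add arm.

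**Working it through.** **The plan's own figures.** The article gives no figure for the imputation. The only related numbers are 44 patients needed and 60 planned, for a "2 (between-subjects, treatment vs. control) × 5 (within-subject, measurements T0–T4) design". As a check on the 44, use the noncentral F for the interaction with λ = f²·N·m·ε/(1 − ρ), m = 5 and f² = 0.03/0.97 = 0.0309. Alpha 0.05, ρ = 0.5 and ε = 1 are assumed, since none is printed. This gives 40. The stated 44 is reached with ρ of 0.45–0.47, with ε = 0.90, or with f cut to 0.17. So 44 is attainable, with inputs that the article does not print. The margin is 1 − 44/60 = 26.7%. It relates to a five-visit design and is used below only as one point in a range.

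**Expected attenuation.** Let δ be the true effect at T1, and m_I and m_C the shares missing in the intervention and control arms. Among observed patients the intervention share is p = (1 − m_I)/[(1 − m_I) + (1 − m_C)]. A pooled regression without arm gives every imputed patient an average shift of pδ. Then:

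- intervention mean shift: (1 − m_I)δ + m_I·pδ
- control mean shift: m_C·pδ
- difference: δ[(1 − m_I) + p(m_I − m_C)]

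With equal missingness this is δ(1 − m): 0.90, 0.80, 0.733 and 0.65 of δ at 10%, 20%, 26.7% and 35%. With 35% missing in the intervention arm and 15% in control, p = 0.65/1.50 = 0.433, and the recovered share is 0.65 + 0.433 × 0.20 = 0.737.

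**Simulation.** 30 per arm (from the article). Assumed: δ = 0.5 SD, T0–T1 correlation 0.5, and missingness unrelated to the scores within arm. 10 imputations, Rubin's rules, 2,000 runs. The imputation model holds sex, age and baseline GSES, with or without arm. The baseline secondary scores are left out for simplicity.

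| Missing at T1 | Effect recovered, no arm | Effect recovered, with arm | Power, no arm | Power, with arm |
|---|---|---|---|---|
| 10% | 0.89 | 0.99–1.01 | 0.42 | 0.52 |
| 20% | 0.79 | 0.99–1.01 | 0.27 | 0.46 |
| 26.7% | 0.72 | 0.99–1.01 | 0.17 | 0.42 |
| 35% | 0.64 | 0.99–1.01 | 0.08 | 0.36 |
| 35% intervention, 15% control | 0.73 | 0.99–1.01 | 0.18 | 0.40 |

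The simulated shares agree with the formula to about 0.01. With a true effect of 0.75 SD and 26.7% missing, the recovered share is again 0.72 without arm, and power is 0.45 against 0.74 with arm.

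**Under no effect.** With 16 of 60 missing and a correlation of 0.6, a nominal 5% test rejected in 0.5% of runs without arm and 5.5% with arm. A second run gave 0.9% and 4.5%. The error is therefore conservative: it costs power and does not inflate false positives.

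**The case against.** **The list may not be exhaustive.** The sentence names fully observed variables that are brought in; it does not say that nothing else enters. The ANCOVA sentence does not name the group factor either, yet it is plainly meant. This is a condensed article, and its data management section refers to a separate statistical analysis plan. If arm is in the model there, the bias vanishes. This lowers confidence that the analysis will go wrong. It does not rescue the printed text: the article chose to print predictors, and the list lacks the variable under test.

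**The trial is exploratory and the bias is conservative.** Both are true, and they limit the harm to underestimation and lost power. That is still a real cost with 60 patients.

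**Stronger readings that the article does not support.** A reader might infer four further faults.

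- *That leaving out later outcomes also shrinks the T1 effect.* It does not; only the absence of arm does. Under permanent dropout, a patient without T1 has no T2–T4 scores to use.
- *That the monotone method does not fit the visits.* Study design sets ordered visits T0 to T4, and with permanent dropout the monotone method suits them. It fails only if patients miss a visit and return, or values are missing irregularly. The article neither shows nor excludes this.
- *That 27% is the planned missingness at T1.* It is a margin inferred from 60 against 44 for a design running through the 12-month follow-up. Missingness at T1, the first visit after treatment, may well be lower.
- *That dropout-assessment scores should be predictors.* Table 1 shows that GSES is not collected there, and only those who withdraw complete it. For patients who leave before T1, the relation of those scores to T1 GSES cannot be estimated.

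**Conclusion.** The point holds in this form: the imputation model as printed omits treatment arm, and following it biases the primary between-group effect toward zero by about the share missing at T1. Over an assumed 10% to 35% missing, the loss is roughly a tenth to over a third of the effect (0.89 down to 0.64 recovered), with power falling from 0.52 to 0.42 at the low end and from 0.36 to 0.08 at the high end. Adding arm removes the bias in every case examined.

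The proportional loss depends mainly on T1 missingness, which is not stated. The power figures also rest on the assumed 0.5 SD effect, the correlation of 0.5 and missingness unrelated to the scores within arm. The conclusion takes the printed list as the working model. If arm is in fact included, what remains is a correction of the text.

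**What to change.** State in Statistical methods, and in the analysis plan, that treatment arm enters the imputation model as a masked code, which keeps the analyst blind, or that imputation is run separately by arm. Keep sex, age and the baseline primary and secondary scores as predictors, and let observed GSES at other visits enter the model. The T1 ANCOVA itself stays unchanged.

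Add one conditional clause: the missing-data pattern is inspected, and if it is not monotone (a missed visit followed by a return), fully conditional specification replaces the monotone method.

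The cost is a sentence or two of text and a software setting. No new data are needed, and the sample size does not change.

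### The T0–T4 mixed ANOVA needs all five scores per patient, and the article leaves open whether, and from what, missing T2–T4 scores are imputed; a mixed model on all observed scores would settle both questions.

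*Protocol article*

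**What the plan says.** All of this is in the protocol article.

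- **Statistical methods, first step.** Efficacy at T1 is analysed by ANCOVA with the T0 score. The next paragraph opens: "First of all, the analyses will be performed according to the intention-to-treat principle". It goes on to say that missing data are imputed by SPSS multiple imputation with a monotone pattern. The inputs it lists are sex, age and the baseline values of the primary and secondary outcomes.
- **Statistical methods, second step.** To judge whether effects last, the arms are compared and "of the different measurement points (T0–T4; with-subject factor) mixed ANOVAs will be conducted". If sphericity fails, "we will use Huynh–Feldt or Greenhouse–Geisser corrections". Nothing here restricts the analysis to completers, and nothing repeats or extends the imputation.
- **Sample size calculation.** Power was computed for a 2 × "5 (within-subject, measurements T0–T4) design where the primary focus was the interaction effect between the treatment and the time variable". The result is that "a total sample of 44 participants is needed". Dropout is called non-negligible without a rate, and "we planned to assign 30 participants to both the treatment and control conditions", 60 in all.
- **Study design.** T2–T4 fall 3, 6 and 12 months after the intervention, and the trial is described as exploratory.

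**The concern.** The sphericity corrections show that the classical mixed ANOVA is meant, not a likelihood-based mixed model. On unimputed data, that method discards a patient's whole record if any one of the five scores is missing, including the scores that were observed. The article expects losses over a follow-up of 12 months after the intervention.

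The handling of missing scores is attached to the first step. A reader cannot tell whether T2–T4 are imputed, or whether a T4 score would be imputed with the help of observed T1–T3 scores.

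At stake is the answer on durability at 3, 6 and 12 months. It could rest on the patients who answered every questionnaire, or on imputations that ignore how patients were doing before they left. Either can distort the arm difference if leaving depends on recent scores differently by arm. That is plausible when patients know whether they receive the intervention or TAU.

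**Working it through.** **1. The plan's own sample size.** The inputs from Sample size calculation are partial η² = 0.03, power 0.80, 2 groups and 5 measurements. Alpha, the correlation between measurements and epsilon are not stated; 0.05, 0.5 and 1 are assumed.

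- f = √(0.03/0.97) = 0.1759.
- The noncentrality is λ = f²·N·m·ε/(1−ρ), with df1 = 4 and df2 = (N−2)·4.
- With f = 0.1759 the smallest even N is 40 (power 0.802).
- With f cut to 0.17 and N = 44, λ = 0.0289 × 44 × 5/0.5 = 12.7, df2 = 168 and power is 0.816. This reproduces the stated 44.

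**2. The margin.** 60 − 44 = 16, and 16/60 = 26.7%. This is the room left in recruitment. It is used below only as an illustrative level of loss.

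**3. If imputation stops at T1 (completer analysis).** If each of T1–T4 is missing independently with probability q (assumed), the share of patients without a full record is 1 − (1−q)⁴:

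- q = 5%: 18.5%
- q = 8%: 28.4%, about 17 of 60
- q = 10%: 34.4%, about 21 of 60

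The next table gives the variance of the arm difference in change from T0 for complete cases, divided by that for a mixed model on all observed scores. It comes from generalised-least-squares information summed over missingness patterns. The assumed correlations are compound symmetry 0.5 or 0.6, or first-order autoregressive 0.8.

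| Missingness (assumed) | Contrast | Variance ratio |
|---|---|---|
| Steady dropout to 26.7% | T4 | 1.09–1.15 |
| Steady dropout to 26.7% | mean of T2–T4 | 1.20–1.21 |
| Steady dropout to 26.7% | T1 | 1.27–1.29 |
| 8% per visit | all three | 1.33–1.38 |
| 10% per visit | all three | 1.43–1.50 |

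**4. Bias at T4.** The simulations use the same correlations. Dropout is set to 26.7%, with its log-odds changing by 1 per SD of the last score. Figures are absolute errors in the T4 − T0 arm difference, in SD units of the score.

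| Method | Low scorers leave one arm only | Low scorers leave TAU, high scorers leave the intervention |
|---|---|---|
| Complete cases | 0.02–0.05 | 0.04–0.08 |
| T4 imputed within arm from baseline only | 0.05–0.08 | 0.10–0.16 |
| Likelihood on all observed scores | under 0.005 | under 0.005 |

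Baseline-only imputation does worse than deletion here because it ignores the post-baseline scores that drive dropout. If earlier visits also enter the imputation, this bias shrinks.

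**5. Scale.** With 22 completers per arm and correlation 0.5 (assumed), the change score has SD √(2 × 0.5) = 1. The standard error of the arm difference is then √(2/22) ≈ 0.30 SD. A bias of 0.08 is about a quarter of this, and 0.16 about a half.

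**The case against.** The article speaks of the analyses in the plural as intention-to-treat and says directly afterwards that missing data are imputed, with no visit or model excluded. On that reading all 60 patients enter the mixed ANOVA. This stands. It rules out the stronger reading that a reader might infer, namely that about 16 of 60 randomised patients will fall out of a result meant to be intention-to-treat. That reading combines two incompatible ones. If intention to treat covers the second step, so does imputation, and nobody is lost. If neither covers it, the long-term result is not declared intention-to-treat. Nor does the article forecast 16 losses, since it states no dropout rate.

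Multiple imputation followed by a complete-data method is a recognised approach. How F tests are combined across imputed data sets is detail that an article may leave to its analysis plan, and each visit contrast can be pooled as a scalar. That stands too, and no finding is made of it.

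The sizes are modest. At T4 under steady dropout, the completer standard error is only about 4–7% larger (√1.09 to √1.15). The largest biases need opposite dropout mechanisms in the two arms. If 44 complete records did remain, that is the number the article says it needs.

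What the objection does not remove is that the named method needs full records, while the imputation described is placed with T1 and lists no post-baseline predictor. An imputation ordered by visit could use earlier visits, but the text does not say so.

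**Conclusion.** The point holds as a recommended improvement to a secondary analysis. As written, the durability comparison is either a completer analysis or one that rests on imputations whose listed inputs stop at baseline. The article does not settle which.

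Under the first reading, the main cost is precision: a variance 9–50% larger across the contrasts and missingness levels assumed, with bias of at most about 0.08 SD. Under the second, all 60 patients are kept, but the T4 arm difference could be off by about 0.05–0.16 SD if later visits really are imputed from baseline alone and dropout depends on recent scores differently by arm. The dropout level, its mechanism and the correlations are all assumptions; the article gives none of them.

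The documents do not show that 16 patients will be excluded, and the primary T1 ANCOVA is not affected by this point.

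**What to change.** In Statistical methods, replace the T0–T4 mixed ANOVAs with a linear mixed model fitted by REML to all observed T0–T4 scores of all randomised patients. Include arm, visit and arm-by-visit, an unstructured covariance and Kenward–Roger degrees of freedom. Name a simpler covariance structure in case of non-convergence. Report the arm difference in change from T0 at each of T1–T4 with a 95% CI, and state that this analysis also follows intention to treat. Keep the mixed ANOVA, if wanted, only as a sensitivity analysis.

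The model uses every observed score and is valid when missingness depends on observed scores. It needs neither imputation of the outcome nor a sphericity correction, so the question of how far the imputation reaches no longer matters for this analysis.

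The cost is a change of wording and a few lines of R, which the abstract already names. No new data are needed. The small downside is that a 5 × 5 unstructured covariance has 5 × 6/2 = 15 parameters to estimate from 60 patients, hence the named fallback.
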